### Statistical analyses: clinical evaluation

The clinical evaluation is conducted according to the intention-to-treat principle. The effectiveness of the group training for primary and secondary outcome measures is analyzed with mixed modeling (i.c. random regression modeling). Baseline measurements, corresponding to the subsequent outcome measurements, are entered as covariables. This method of mixed modeling for repeated measurements enables the use of flexible error covariance structures. In addition, the predictive performance of baseline-variables, especially personality variables, on effectiveness can be estimated.

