Patients are recruited from general practices and outpatient clinics of general hospitals in and nearby Rotterdam, the Netherlands. Physicians' attention is drawn to the group training by periodical postcards informing them when and how they can refer patients to the group training. Patients' attention is drawn to the group training by announcements in local newspapers and on websites of patients' associations, in which they are asked to make an appointment with their physician to discuss referral when interested. Physicians decide whether the physical symptoms are medically explained or unexplained hereby checking the first exclusion criterion, after which they refer patients when they find this appropriate. After referral, patients are invited for an interview, preferably in a medical setting, in which they are verbally and in writing informed about the study. In this interview, the first three inclusion criteria and the last exclusion criterion are verified. After receiving patients' signed informed consent, patients are invited for a second interview, in which the last inclusion criterion and the second exclusion criterion are investigated by the Structured Clinical Interview for DSM-IV Axis I Disorders/Patient edition (SCID-I/P) administered by independent psychologists. These psychologists make the final decision based on the results of the SCID-I/P whether patients' UPS can be classified as an undifferentiated somatoform disorder or as a chronic pain disorder and whether this disorder is the principal DSM-IV-TR classification. If undifferentiated somatoform disorder or chronic pain disorder is the principal DSM-IV-TR classification, then patients complete the self-report questionnaire for DSM-IV Axis II personality disorders (VKP).

Right before the start of each next training, the newly included patients fill in the questionnaires. Subsequently, an independent statistician randomizes them to either the group training or waiting list with a computer-based 1:1 ratio randomization procedure. The results of this randomization procedure are sent to the patient by letter. If randomization leads to starting with the group training, then an invitation for the group training is enclosed in the randomization letter. After the group training or after a waiting-period of the same length as the group training, all patients fill in the questionnaires for the second time.

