After filling in the outcome measurements for the second time, the patients on the waiting list are invited to the group training. They follow the group training after their waiting period together with the newly included patients randomized to the group training in the most recent randomization. For patients on the waiting list, a longer waiting period is not feasible, because the study is conducted in the daily practice of a real life mental healthcare institution. By combining the patients assigned by the previous randomization to the waiting list with the patients assigned by the next randomization to the group training in the same training, the patients in both conditions receive exactly the same training. After completing the training, all patients fill in follow-up measurements after three months and after one year.

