**Figure 2 F2:**
[figure not shown]
**Modified consequences model based on Speckens et al**. [18,19].

We assume that this original consequences model has not completely succeeded in preventing the 'its all in the head' suggestion. After all, patients might perceive the focus on irrational beliefs still as 'its all in the head'. Patients might experience the disputing of these beliefs as blaming and belittling. Blaming and belittling result in a rejection of the therapy by patients and in poor outcome [20,21]. That is why we modify the consequences model for our group training (see red arrows in Figure 2). Our group training focuses on the visible consequences, labeling them as survival strategies in reaction to physical symptoms, justifying their existence by their benefit in short term, albeit indicating their harmfulness in the long run and therefore replacing them with long run beneficial strategies. Subsequently, the underlying beliefs of these survival strategies are explored, checked and, if necessary, changed in more helpful ones. Finally, the problem-solving model of Nezu *et al*. [22] is introduced to facilitate developing personal effective survival strategies for all kinds of problems, acknowledging that physical symptoms can increase the number of problems. The ultimate goal is not aimed at reducing physical symptoms as with the original consequences model, but is aimed at improving quality of life.

In summary, the group training uses the consequences model bottom-up instead of the commonly used top-down approach. By using the consequences model bottom-up (starting with consequences and unconditionally accepting and justifying their existence) instead of top-down (starting with addressing irrational beliefs and disputing them), we reach a closer match with the patients' physical point of view. Moreover, patients are relieved from being blamed, called exoneration, by justifying the existence of consequences by their benefit in short term, by which we facilitate compliance. Furthermore, we tailor the setting of the training to patients' physical point of view by organizing the training in a medical healthcare setting and not in our own mental healthcare institution. Herewith, also the implicit but unintended 'its all in the head' suggestion is avoided.

This bottom-up strategy results in a group training comprising thirteen ad verbatim protocollized weekly sessions of two hours each.

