### Sample size calculation

To determine the required sample size for measuring differences in quality of life between the two conditions (group training and waiting list), the sample size is calculated by power analysis. The effect size of cognitive behavioral therapy for quality of life is not well known, because in other effect studies the outcome is usually measured in terms of physical symptoms. Therefore, we have to use effect size of cognitive behavioral therapy for physical symptoms as an available estimator for the (shortage of) quality of life. The effect size of cognitive behavioral therapy for physical symptoms ranges from .00 to .95 [8], suggesting a medium effect for cognitive behavioral therapy for physical symptoms. Assuming this effect also applies for quality of life, the magnitude of the effect size following Cohen's (1988) [28] is 0.50. With a power of .80 and an alpha of .05 (two-tailed), a sample size of 100 patients (50 in each condition) is required.

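### The mixed model is described as handling only repeated measurements within a patient, although training is delivered in groups to one arm only and patients are randomised in batches; the training group and the batch should be named in the model.

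*Protocol article*

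**What the plan says.** **Analysis.** The section on statistical analyses for the clinical evaluation names an intention-to-treat mixed (random regression) model with the baseline value of each outcome as covariate. On correlation it says only: "This method of mixed modeling for repeated measurements enables the use of flexible error covariance structures". It names no effect for training group or randomisation batch. The general statistical section adds covariates only when the arms turn out not to be comparable on a baseline variable.

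**Delivery.** The experimental condition is a "group training comprising thirteen ad verbatim protocollized weekly sessions of two hours each". The control condition is a wait of the same 13 weeks, with no group contact described.

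**Randomisation.** Patients are randomised individually but in successive rounds: "Right before the start of each next training, the newly included patients fill in the questionnaires", after which "an independent statistician randomizes them to either the group training or waiting list with a computer-based 1:1 ratio randomization procedure". Once their second questionnaires are completed, waiting-list patients are trained: "They follow the group training after their waiting period together with the newly included patients randomized to the group training" in the next round.

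**Sample size.** The calculation gives its inputs in full (effect size 0.50, power 0.80, two-tailed alpha 0.05, 50 per arm) and contains no allowance for clustering.

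**Length of the controlled comparison.** The economic analysis section says the arms can be compared empirically only up to 13 weeks. The Discussion says the follow-up measurements have no control condition.

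**The concern.** Patients in one training group share their fellow trainees, the sessions and the weekly exchange of experiences, so their 13-week scores may be correlated. A covariance structure across one patient's time points cannot absorb correlation between different patients. At 13 weeks the grouping exists in the training arm only. The variance of that arm's mean is then larger than a model with patient-level terms alone assumes, while the waiting-list variance is not inflated in this way. The primary contrast would have confidence intervals that are too narrow and a test that can reject too often.

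Randomisation batch is a second feature of the design that the described model does not mention. Inclusion ran from February 2005 to September 2008, so batches may differ in referral mix or season. Leaving batch out mainly loses precision.

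**Working it through.** **The plan's own figure.** Normal approximation, two-sided: n per arm = 2(1.960 + 0.842)² / 0.50² = 62.8, so 63 (64 with the t-test), against the 50 stated. Power at 50 per arm is Φ(0.50/√(2/50) − 1.960) = Φ(0.540) = 0.705. The stated 100 is therefore not reproduced, even with independent patients. That is a separate matter; it appears here only because 0.705 is the starting point for the power column below.

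**Group size.** February 2005 to September 2008 is about 43 months. 43 × (52/12) / 13 ≈ 14.3, so at most about 14 successive 13-week rounds if one group runs at a time. 50/14.3 ≈ 3.5 training-arm patients per group. Fewer rounds would mean larger groups, so 8 per group (about six groups) is also shown. Only training-arm patients count here: the waiting-list patients who join a group have already given their 13-week measurement.

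**Formula.** With m training-arm patients per group, an ICC in the training arm only, and n per arm:

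- Var(difference) = (σ²/n) × [1 + (m − 1)ICC + 1]
- naive SE / true SE = √(2 / [2 + (m − 1)ICC])
- type I error = 2[1 − Φ(1.960 × that ratio)]
- power at d = 0.50 = Φ(0.50 / √([2 + (m − 1)ICC]/50) − 1.960)

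For example, with m = 8 and ICC = 0.10: √(2/2.7) = 0.861, an understatement of 13.9%; type I error 2[1 − Φ(1.687)] = 0.092.

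| m | ICC | SE too small by | Type I error | Power, 50 per arm |
|---|---|---|---|---|
| 3.5 | 0.01 | 0.6% | 0.051 | 0.700 |
| 3.5 | 0.10 | 5.7% | 0.065 | 0.654 |
| 4 | 0.05 | 3.6% | 0.059 | 0.674 |
| 4 | 0.10 | 6.7% | 0.068 | 0.645 |
| 8 | 0.01 | 1.7% | 0.054 | 0.691 |
| 8 | 0.05 | 7.7% | 0.071 | 0.635 |
| 8 | 0.10 | 13.9% | 0.092 | 0.576 |

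Both m and ICC are assumptions. The number of sessions does not enter the formula.

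**Adding batch.** A simulation (20,000 runs per setting, two-sample t-test, no baseline covariate, exact 1:1 balance within each batch) gave these naive/true SE ratios. Columns show the share of variance assigned to batch and to training group.

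| Groups × size | Batch | Group | SE ratio | Type I error |
|---|---|---|---|---|
| 13 × 4 | 0.10 | 0 | 1.045 | 0.039 |
| 13 × 4 | 0 | 0.05 | 0.962 | 0.058 |
| 13 × 4 | 0.10 | 0.05 | 1.001 | 0.050 |
| 13 × 4 | 0.05 | 0.10 | 0.952 | 0.061 |
| 10 × 5 | 0.10 | 0.05 | 0.995 | 0.051 |
| 10 × 5 | 0.05 | 0.10 | 0.924 | 0.070 |
| 5 × 10 | 0.05 | 0.10 | 0.839 | 0.098 |

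Over all settings with batch alone omitted, the ratio was 1.018 to 1.049 and the type I error 0.038 to 0.045, which is conservative. With both omitted the net ratio ran from 0.839 to 1.001. The lowest value needs ten training-arm patients per group, more than the 3.5 to 8 taken above.

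**The case against.** **The article may only be silent.** A mixed model can carry a training-group intercept, the article does not list its random effects, and a condensed article may leave them to a fuller plan. This has weight. A reader might infer that the protocol treats trained patients as independent; it nowhere says so, and it excludes no group term. But where the text does describe the correlation the model handles, it names repeated measurements. The sample size calculation has no clustering allowance, and the Discussion weighs the design's limitations without mentioning grouping. Run as described, the model leaves the group out.

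**Batch.** A reader might also infer that ignoring batch makes standard errors too small. The documents do not support this. Allocation is 1:1 at each round, so batch should be roughly balanced between arms, and omitting it then makes the naive standard error too large. The article does not say that allocation is blocked, so exact balance is an assumption of the simulation.

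**Offsetting.** The two omissions can cancel, as in the 13 × 4 setting with ratio 1.001. An excess over 5% is therefore possible but not certain. Equally, cancellation depends on unknown variance shares and should not be relied on.

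**Follow-up.** Training groups later mix patients from both arms. A reader might conclude that this disturbs the primary comparison. It cannot, because the randomised contrast ends at 13 weeks.

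**Limits of the check.** The calculations omit the planned baseline covariate, so the ICC should be read as the correlation left after baseline adjustment. That value is unknown and may be small.

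**Conclusion.** The point stands as a recommended change to the analysis text, with medium confidence. The training arm is grouped and the waiting list is not, and the only dependence the plan describes is within a patient. With a positive group correlation that omitted batch variance does not offset, the 13-week standard error is too small.

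Considering the group omission alone, the understatement is about 1-7% if about 14 rounds give 3.5-4 training-arm patients per group (ICC 0.01-0.10), and reaches about 14% only with 8 per group at ICC 0.10. The drop in power that belongs to this point is the fall from 0.705 to between 0.700 and 0.576 in the same settings; the shortfall from 0.80 to 0.705 does not belong to it. All of these sizes rest on assumed group sizes and ICCs.

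**What to change.** In the section on statistical analyses for the clinical evaluation, state that the 13-week model includes:

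- a random effect for training group that applies to training-arm patients only (partially nested model);
- randomisation batch as a stratification term in both arms;
- Satterthwaite or Kenward-Roger degrees of freedom.

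For the uncontrolled follow-up analyses, assign every patient the random effect of the group in which that patient was actually trained.

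This changes wording only: group and batch membership follow from the conduct of the trial, and no new data are needed. The cost is slightly wider intervals and fewer degrees of freedom. At 13 weeks all training-arm patients of one group come from one batch, so group and batch can be separated only through that batch's waiting-list patients. With roughly 6 to 14 groups the group variance will be estimated imprecisely, so its estimate should be reported with its uncertainty.

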### Statistical analyses: economic evaluation

The economic evaluation is conducted from a societal perspective, the preferred perspective in health economic evaluations [29]. This means that all costs are included: the direct medical costs, the indirect medical costs and the indirect costs associated with productivity loss of patients. Adopting a societal perspective also means that all relevant effects and all costs beyond the time frame of the trial should be measured. In this case, the differences between group training and waiting list can only be measured empirically till 13 weeks, but relevant effects and costs might occur beyond that artificial time horizon. For this reason, we will estimate effects and costs till 2 years, using a Markov model [30]. By making the Markov model probabilistic, we will be able to implement multiple sensitivity tests simultaneously and test for specific model assumptions. A critical assumption will be the extrapolation of the effect beyond 13 weeks. This assumption will be explored by calculating the minimal duration that the group training should be effective, in order to achieve a satisfactory level of cost-effectiveness.

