### Outcome measurements

(Cost-)effectiveness is measured with three self-report questionnaires, which are sent to patients' home to be completed before randomization, at the end of the training or waiting list period, after 3 and 12 months after the training (see Figure 1).

1) Short Form Health Survey (SF-36) [23]

The SF-36 measures functional health and well-being during the past four weeks with the following eight multi-item scales: Physical functioning, Role functioning physical, Bodily pain, General health, Vitality, Social functioning, Role functioning emotional and Mental health. The scores of the SF-36 can also be summarized in the Mental and the Physical summary scores [24]. Furthermore, a utility score can be derived from 11 items of the SF-36. These 11 items define six dimensions of health, the SF-6D; Physical functioning, Role limitations (Role functioning physical in combination with Role functioning emotional), Bodily pain, Social functioning, Vitality and Mental health. The outcome of the SF-6D can be converted into Quality Adjusted Life Years (QALYs), the preferred outcome in health economics, using formerly called 'valuations studies' [25].

2) Symptom Checklist Revised (SCL-90-R) [26]

The SCL-90-R measures a broad range of symptoms and their intensity during the past week with the following eight multi-item scales: Phobic anxiety, Anxiety, Depression, Somatization, Obsessive-compulsive, Interpersonal sensitivity, Hostility and Sleep difficulties. The scores of the SCL-90-R can be summarized in the Global severity index, reflecting the overall psychological distress.

3) Trimbos/iMTA Questionnaire for Costs associated with Psychiatric Illness (TiC-P) [27]

The TiC-P measures direct medical costs due to healthcare utilization during the past four weeks, excluding the group training itself. The costs of the training itself are calculated using the records of the institution. The TiC-P also registers the indirect non-medical costs due to productivity loss during the past two weeks. This second part of the questionnaire about indirect costs is based on the short form of the Health and Labour Questionnaire (HLQ).

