### Outcome measurements: economic evaluation

The aim of the economic evaluation is to investigate cost-effectiveness of the group training in terms of cost per Quality Adjusted Life Years (QALYs). QALYs are estimated by converting SF-6D into utilities by means of the preference-based UK tariff [25]. Indirect costs for employed patients are measured with the TiC-P by the reported duration of sick leave and the production loss without sick leave. The indirect costs of production loss due to sick leave are computed by multiplying the number of sick leave's day with the average net income per worker related to age and gender. By a long-term sick leave, the friction-cost method is applied to assess the productivity loss, using a friction period of 5 months.

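### The economic evaluation claims to include all societal costs but leaves out patients' travel and session time, which only the training arm bears during the controlled 13 weeks

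*Protocol article*

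**What the plan says.** Under 'Statistical analyses: economic evaluation' the protocol article states: "The economic evaluation is conducted from a societal perspective". It explains that this means "all costs are included: the direct medical costs, the indirect medical costs and the indirect costs associated with productivity loss of patients". That is a list of three categories.

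The sources are described in two other sections.

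- **Care other than the training** ('Outcome measurements'): "The TiC-P measures direct medical costs due to healthcare utilization during the past four weeks, excluding the group training itself".
- **The training** (same section): "The costs of the training itself are calculated using the records of the institution".
- **Work loss** (same section): "The TiC-P also registers the indirect non-medical costs due to productivity loss during the past two weeks". 'Outcome measurements: economic evaluation' adds: "Indirect costs for employed patients are measured with the TiC-P by the reported duration of sick leave and the production loss without sick leave".

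The training is 13 weekly sessions of two hours, held in a medical setting away from the institution's own premises ('Experimental condition: group training'). Patients on the waiting list wait out those 13 weeks before starting ('Control condition: waiting list'). Costs and effects are then modelled to 2 years. One planned output is the shortest duration of effect at which the training would be satisfactorily cost-effective.

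**The concern.** A societal perspective counts costs whoever bears them. A patient who travels to 13 sessions and spends two hours in each bears a real cost, and this cost belongs to none of the three listed categories. It is not medical care, it is not a provider cost found in the institution's records, and for most patients and most sessions it is not productivity loss as measured.

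This is more than an incomplete list, because the omission is one-sided. In the only period with a randomized control, one arm attends sessions and the other does not. Leaving the item out therefore lowers the cost difference between arms and cannot raise it. The cost per QALY is too low by the omitted amount divided by the QALY gain, and the minimal duration of effect comes out too short. Cost-effectiveness is part of the stated primary aim, so the error would reach a main conclusion. The SF-36 primary outcome is not affected.

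**Working it through.** The article states no figure for this item, so there is none to reproduce. The check has two parts: whether any stated source could capture the cost, and how large it could be.

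**Coverage**

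- *Travel cost:* not in the list of categories, the questionnaire content as described, or the institution's records as described.
- *Session time, patients not in work:* no source, because indirect costs are measured for employed patients.
- *Session time, employed patients:* absence from work to attend could appear as work loss. The recall is two weeks, which reaches about 2 of the 13 weekly sessions.

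**Quantity, from the article**

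- Training arm: 13 × 2 h = 26 session hours per patient. Waiting list over the same 13 weeks: 0.

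**Size, on assumed values not in the article**

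Assumptions: 0.5 to 1.0 h travel per session, EUR 5 to 25 per hour of patient time, EUR 3 to 10 per session in travel expense.

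- Hours: 26 + 13 × 0.5 = 32.5, up to 26 + 13 × 1.0 = 39.
- Time cost: 32.5 × 5 = EUR 162.50, up to 39 × 25 = EUR 975.
- Travel expense: 13 × 3 = EUR 39, up to 13 × 10 = EUR 130.
- Total: EUR 201.50 to EUR 1,105 per trained patient.

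**Effect on cost per QALY over the planned 2 years**

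Assume a utility gain of 0.05, reached linearly by week 13 (0.25 year).

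- Gain held for the full 2 years: 0.05 × 0.25 / 2 + 0.05 × 1.75 = 0.00625 + 0.0875 = 0.09375 QALY. Added cost per QALY: 201.50 / 0.09375 = EUR 2,149, up to 1,105 / 0.09375 = EUR 11,787.
- Of that, travel expense alone: 39 / 0.09375 = EUR 416, up to 130 / 0.09375 = EUR 1,387.
- Gain lost after 1 year: 0.00625 + 0.05 × 0.75 = 0.04375 QALY. Added cost per QALY: 201.50 / 0.04375 = EUR 4,606, up to 1,105 / 0.04375 = EUR 25,257.

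**Effect on the minimal duration**

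With a constant gain of 0.05 and no other cost change, the extra duration needed is the omitted cost divided by (threshold × 0.05).

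- Assumed threshold EUR 20,000 per QALY: 201.50 / 1,000 = 0.20 year (2.4 months), up to 1,105 / 1,000 = 1.1 years (13 months).
- Assumed threshold EUR 80,000 per QALY: 201.50 / 4,000 = 0.05 year (0.6 month), up to 1,105 / 4,000 = 0.28 year (3.3 months).

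**The case against.** The strongest reply is that the amount may be modest and is partly caught. Work missed for sessions can enter the productivity questions for employed patients. If the two-week report were scaled up to 13 weeks, adding all 26 hours on top would count some of it twice. Most of the assumed total is also time rather than travel expense, and the unit values are not in the article. These points stand. They limit how time should be added, but they do not supply a source for travel cost or for the time of patients not in work, and they do not change the direction.

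Three stronger readings are tempting, and the document does not support them.

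- *Most of the controlled period is left uncosted.* The end-of-period questionnaire looks back 4 weeks for care and 2 weeks for work, so 9/13 (69%) and 11/13 (85%) of the weeks fall outside it. Those weeks are unobserved. Nothing says that they are set to zero, and an article may leave the scaling or interpolation rule to the full protocol or analysis plan.
- *The recall gap favours the training.* The windows are the same in both arms, and the direction depends on time course and scaling. In units of the full weekly saving, a saving that builds linearly totals 6.5. Scaling the windows gives 13 × 11/13 = 11.0 (4 weeks) or 13 × 12/13 = 12.0 (2 weeks), which flatters the training. A saving that fades linearly also totals 6.5, but scaling gives 2.0 or 1.0, which works against it. A constant saving is scaled without bias.
- *The indirect medical costs named in the analysis section contradict the measurement section.* No source is named for them, but the term could refer to costs in the 2-year model. No effect on the result can be shown.

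**Conclusion.** The claim of complete societal costs does not match the article's own categories and sources. Patients' travel and session time are missing and fall on the training arm alone during the controlled period, so the plan as written tilts cost per QALY and the minimal duration of effect towards the training.

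The direction needs no assumption beyond a positive price for travel or time. The size rests wholly on assumed values: about EUR 200 to 1,100 per trained patient, or roughly EUR 2,000 to 12,000 per QALY if a 0.05 utility gain lasted 2 years, and more if it faded sooner. Dividing by the 13-week QALY gain alone would give far larger figures, but that is not the planned horizon and should not be used as the headline. The point concerns the economic evaluation only.

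**What to change.** 1. Add patient travel to the cost of the training in the base case: sessions attended times a standard unit price per trip. Use 13 sessions if attendance per patient was not recorded, since the article refers to institutional records without saying that they hold attendance.
2. Add patient time (session plus travel) at a stated unit price as a sensitivity analysis, leaving out working hours already counted as productivity loss. Carry both items into the probabilistic model and the minimal-duration analysis.
3. If this is not done, withdraw the statement that all costs are included and the claim to a full societal perspective, and name the costs left out.

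Inclusion has already closed, but no new questionnaire is needed. The change takes a few unit prices and one costing rule. Travel would probably have to be imputed rather than measured, and the cost per QALY will be less favourable to the training.

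### QALYs and costs get at most a test-gated baseline adjustment, while every clinical outcome is always adjusted for its own baseline

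*Protocol article*

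**What the plan says.** Three sections of the protocol article bear on this.

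- **Statistical analyses (general).** Baseline variables are compared between arms with t-tests, Mann-Whitney tests or chi-square tests. Variables on which the arms are not comparable become covariates in the later analyses. The section precedes both evaluations, so read literally it covers the economic one.
- **Statistical analyses: clinical evaluation.** "Baseline measurements, corresponding to the subsequent outcome measurements, are entered as covariables". No condition is attached. The sentence concerns the primary and secondary outcomes, which Outcome measurements: clinical evaluation defines as SF-36 and SCL-90-R scores. QALYs and costs are not among them.
- **Statistical analyses: economic evaluation.** "we will estimate effects and costs till 2 years, using a Markov model". The model is probabilistic. The section notes that "the differences between group training and waiting list can only be measured empirically till 13 weeks". It names no baseline term for QALYs or costs and does not describe how the 13-week inputs are formed.

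On the data, "QALYs are estimated by converting SF-6D into utilities by means of the preference-based UK tariff", and the SF-6D comes from SF-36 items. Under Outcome measurements, the SF-36 and the TiC-P cost questionnaire are both "sent to patients' home to be completed before randomization, at the end of the training or waiting list period". Each patient's baseline utility and baseline cost are therefore available.

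**The concern.** The plan states two rules for outcomes taken from the same questionnaire. SF-36 summary scores are always adjusted for their own baseline. SF-6D utilities are adjusted only if a baseline test finds the arms different.

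A significance test is a poor gate for this purpose. What matters is how strongly baseline predicts the outcome and how large the imbalance is relative to the expected effect, and a test with 50 per arm measures neither. If the rule is followed as written, imbalances short of significance stay in the estimate and precision already paid for is lost.

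Cost-effectiveness is part of the primary aim. Thirteen weeks is the only controlled period, and the model extends it to 2 years. Error in the 13-week inputs is therefore carried forward. Making the model probabilistic expresses the uncertainty but does not remove an imbalance.

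**Working it through.** **Inputs from the protocol article.** 50 per arm (Sample size calculation; "computer-based 1:1 ratio randomization procedure" under Study population). Standardised effect: "the magnitude of the effect size following Cohen's (1988) [28] is 0.50". Controlled period 13 weeks, T = 0.25 year.

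**The plan's own figure.** The article states: "With a power of .80 and an alpha of .05 (two-tailed), a sample size of 100 patients (50 in each condition) is required". With d = 0.50 the normal approximation gives 2 × (1.960 + 0.842)² / 0.50² = 62.8, so 63 per arm (126 in total; 128 with the t-test). With 50 per arm, power is about 0.70. The stated 100 does not reproduce as a two-tailed calculation. That is a separate matter; only d and n are used below.

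**Assumptions not in the article.** The d of 0.50 applies to SF-6D utility. The baseline-to-13-week correlation r is 0.3 to 0.7. The utility SD is equal at both times; where an absolute value is needed, it is 0.12. The baseline test uses the 0.05 level.

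**Chance baseline difference.** Its standard error is √(2/50) = 0.20 SD. A t-test on 98 degrees of freedom flags only differences above 1.984 × 0.20 = 0.40 SD. A one-standard-error difference (p about 0.32) is never flagged.

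**Case A: 13-week utility is the input.**
- Adjusted over unadjusted SE = √(1 − r²).
- Shift from a one-SE imbalance, relative to the effect = r × 0.20/0.50 = 0.4r.
- In absolute terms at r = 0.6, SD 0.12 and an assumed gain of 0.05: imbalance 0.12 × 0.20 = 0.024; shift 0.6 × 0.024 = 0.0144; 0.0144/0.05 = 29%. An assumed gain of 0.05 is d = 0.05/0.12 = 0.42, so this figure is a little above the 24% at d = 0.50.

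**Case B: two-point linear area under the curve.**
- Gain = (T/2) × 0.50 SD = 0.0625 SD.
- Shift relative to the gain = (1 + r) × 0.20/0.50 = 0.4(1 + r).
- SE relative to the gain: unadjusted 0.4√(2(1 + r)); adjusted 0.4√(1 − r²). The utility SD cancels.

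| r | A: SE reduction | A: one-SE shift | B: one-SE shift | B: SE/gain, unadjusted → adjusted |
|---|---|---|---|---|
| 0.3 | 5% | 12% | 52% | 0.65 → 0.38 |
| 0.5 | 13% | 20% | 60% | 0.69 → 0.35 |
| 0.6 | 20% | 24% | 64% | 0.72 → 0.32 |
| 0.7 | 29% | 28% | 68% | 0.74 → 0.29 |

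In case B, power for the QALY difference at r = 0.5 rises from 0.30 to 0.82 with adjustment.

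**Just under the flag.** Multiplying the one-SE shifts by 1.984 gives 40%, 48% and 56% in case A at r = 0.5, 0.6 and 0.7, and 103%, 119% and 135% in case B at r = 0.3, 0.5 and 0.7. In case B, the probability of an imbalance that is both unflagged and at least as large as the gain is about 1%, 5% and 9% at those same three correlations.

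**Case C: change from baseline.** Adjustment lowers the SE by 1 − √((1 + r)/2) = 11% at r = 0.6. A one-SE imbalance over-corrects by 0.4 × 0.024/0.05 = 19% of the assumed gain.

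**Costs.** The article gives no cost SD or correlation, so no magnitude can be computed.

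**The case against.** The strongest reply is that the economic section is silent rather than wrong. It never says that QALYs and costs are left unadjusted. A condensed article may leave the regression behind the model inputs to a fuller document, and the general covariate rule already reaches the economic evaluation. The abstract speaks of analyzing differences between measurements, and the discussion plans to study baseline variables as predictors of cost-effectiveness. Randomization also makes the unadjusted comparison unbiased on average.

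Much of this stands. A reader might infer that the plan does not adjust QALYs and costs, or enters them as observed; the text supports neither. A reader might also infer that imbalance will swamp the QALY gain. That needs an unadjusted two-point area under the curve, which the article never specifies, and even then an unflagged imbalance as large as the gain has a probability of only about 1-9%. Nor should the case B percentages be carried over 2 years: after 13 weeks baseline utility no longer forms part of the area, and the difference carried forward is the case A one.

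What does not stand is that silence settles the point. The article does state a rule for the later analyses, and that rule is gated by a test. Analyzing predictors is not the same as adjusting the treatment contrast for the outcome's own baseline. Unbiasedness on average does not recover the lost precision or correct the imbalance in the one sample observed.

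**Conclusion.** The point holds in a limited form. Unconditional own-baseline adjustment is stated for clinical outcomes only. QALYs and costs have at most a test-gated rule that leaves non-significant imbalances in, although the baseline values needed are collected.

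The consequence is mainly lost precision, plus a conditional shift when the arms differ by chance. For a 13-week utility input at r = 0.6, the SE is about 20% lower with adjustment (13-29% for r of 0.5-0.7), and a one-SE imbalance otherwise moves the difference by about 29% of an assumed 0.05 gain. For a two-point area-under-the-curve QALY at d = 0.50, the shift is 52-68% of the gain (r of 0.3-0.7) and adjustment roughly halves the SE. All of this rests on assumed correlations, on applying d = 0.50 or a 0.05 gain to the SF-6D, and on a choice of input that the article leaves open. The effect on costs cannot be quantified.

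**What to change.** Add to Statistical analyses: economic evaluation: The 13-week utility (or QALY) and cost differences entering the probabilistic model are estimated with baseline SF-6D utility and baseline TiC-P cost, respectively, as covariates, whatever the baseline comparison shows, and their uncertainty is carried into the model. State in the same place whether the utility input is the 13-week value or an area under the curve.

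This extends to the economic inputs the rule already in force for the clinical outcomes. It costs a sentence or two and one regression per input, with no new data and no extra patients.
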